**Table d95e520:** 

p_1_≥α_0_=0.3	: stop because of futility
p_1_ϵ (0.0299; 0.3)	: continue with stage II
p_1_≤α_1_=0.0299	: stop with success (rejection of H_0_)

Decision Structure for Stage II results (two-sided)

**Table d95e551:** 

p_1_p_2_>α_c_=0.0087	: stop because of futility
p_1_p_2_≤α_c_	: rejection of H_o_ (proof of efficacy)

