#### Two-Stage Procedure

The two-stage adaptive procedure of Bauer P and Köhne K (1994) is chosen as the sequential method. The two-stage procedure based on Fisher’s combination test (Bauer and Köhne) shows only a negligible loss in test power as compared to a fixed sample size study but allows early stopping due to success or failure [37]. Furthermore, assumptions for sample size calculation can be rechecked after stage I. The same applies to design modifications within the framework of the adaptive approach, although this is not the rationale for introducing the two-stage procedure in this study. The formal Bauer-Köhne *futility* benchmark is set for this study to α_0_=0.3. It is important to note that this benchmark takes into account the limited number of available patients for a possible stage II due to the restricted cohort design.

With a global multiple level alpha=0.05 two-sided, and defined futility level of α_0_=0.3 the following decision structure will be formally established (p_1_=P-value of stage I, p_2_=P-value of stage II):

Decision Structure for Stage I results (two-sided)

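### The stage II rule multiplies two-sided p-values with no condition on direction, so two stages pointing opposite ways can count as proof of efficacy

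*Protocol article*

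**What the plan says.** The section Two-Stage Procedure of the protocol article adopts Bauer-Köhne: "The two-stage procedure based on Fisher’s combination test (Bauer and Köhne"). It fixes the error level as "With a global multiple level alpha=0.05 two-sided" with futility level 0.3, and defines p1 and p2 only as the P-values of stages I and II.

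Two decision tables follow.

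- **Stage I**, headed "Decision Structure for Stage I results (two-sided"): the futility line is "p_1_≥α_0_=0.3". The line "p_1_≤α_1_=0.0299" leads to "stop with success (rejection of H_0"). Values between the two continue to stage II.
- **Stage II**, headed "Decision Structure for Stage II results (two-sided"): a product above 0.0087 stops for futility. A product at or below it gives "rejection of H_o_ (proof of efficacy").

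Neither table mentions the sign of the effect, MW > 0.5, or agreement between stages. The section Effectiveness Evaluation calls the comparison a superiority test and opens the secondary outcomes only if that test is significant. It also has MW and its confidence interval reported with each P-value to show direction. It does not make that direction part of the decision rule. The formula for the hypotheses is in a figure that is not shown.

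**The concern.** A two-sided p-value measures distance from the null and carries no sign. In a single-stage trial this is harmless, because the one estimate behind the p-value supplies the sign. In a combination test there are two estimates, and a product of two-sided p-values is equally small whether they agree or contradict each other.

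The rule can therefore reject on contradictory stages and label the result as efficacy. The rejection would also open the fixed sequence of secondary outcomes. The risk lies where the true effect is null or small, which is where a confirmatory rule has to be reliable.

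**Working it through.** **Inputs.** From Two-Stage Procedure and its tables: alpha = 0.05 two-sided, α0 = 0.3, α1 = 0.0299, αc = 0.0087. From Sample Size: MW = 0.55, allocation 1:2 at worst, stage I = 30% of the total, N = 1745 (about 2000 after the 15% allowance).

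**1. The article's own bounds.**
- αc = exp(−χ²(4; 0.95)/2) = exp(−9.488/2) = 0.0087.
- α1 solves α1 + αc·ln(α0/α1) = 0.05, which gives 0.0299.

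Both agree with the tables, so the bounds are correct for alpha 0.05 applied to the stated p-values.

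**2. A discordant example.**
- p1 = 0.10 favouring Cerebrolysin: Z1 = +1.645.
- p2 = 0.05 favouring control: Z2 = −1.960.
- p1 lies between 0.0299 and 0.3, so the study continues.
- p1·p2 = 0.005 ≤ 0.0087, so the efficacy line is met.
- Pooled Z = √0.3 × 1.645 + √0.7 × (−1.960) = 0.901 − 1.640 = −0.74, towards control.

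**3. Null rejection probability split by direction.** Under no effect the sign is independent of the two-sided p-value.
- Stage I: 0.0299, that is 0.0299/2 = 0.01495 in each direction.
- Stage II: 0.0087 × ln(0.3/0.0299) = 0.0201, that is 0.0050 for each of the four sign patterns.

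| Rejection under no effect | Probability |
|---|---|
| Stage I, favours Cerebrolysin | 1.5% |
| Stage I, favours control | 1.5% |
| Stage II, both favour Cerebrolysin | 0.5% |
| Stage II, both favour control | 0.5% |
| Stage II, opposite directions | 1.0% |
| Total | 5.0% |

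Half of the stage II rejections (1.0 of 2.0 points) are discordant. A simulation of 4 million null trials gave 5.0% in total and 1.0% discordant.

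**4. At the planned effect.** Noether approximation without tie correction, with mean Z = (MW − 0.5)·√(12·t(1−t)·n) and t = 1/3. For N = 1745 the mean is 1.87 at stage I (n = 0.3N) and 2.85 at stage II (n = 0.7N). Discordant rejection then has probability about 0.15%, nearly all of it stage I towards control and stage II towards Cerebrolysin. Stage I rejection favouring control is about 0.003%.

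**5. One-sided version.** With alpha = 0.025 and α0 = 0.15 (the favourable half of the present 0.3):
- αc = exp(−χ²(4; 0.975)/2) = exp(−11.143/2) = 0.0038.
- α1 solves α1 + 0.0038·ln(0.15/α1) = 0.025, which gives 0.0166.

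On the same approximation, the probability of a consistently favourable rejection compares as follows:

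| N | Present bounds | One-sided 0.025 |
|---|---|---|
| 1745 | 74.2% | 76.2% |
| 2000 | 79.5% | 81.0% |

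These figures serve only to compare the two rules. The article's 90% comes from planning software whose method is not shown.

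**The case against.** The tables are not read alone. The article calls the test one of superiority, defines MW as the chance that a treated subject does better, and reports MW with its interval so that direction is visible. Reading direction from the estimate after a two-sided test is normal practice. The unseen hypothesis figure may also state a direction.

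Much of this stands, and it limits three stronger readings.

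- **A reader might infer that type I error is inflated.** It is not: the total is 0.05 and the bounds are right. If direction were taken from the 30/70 pooled Z, discordant null rejections would split about 0.5% to 0.5%. The favourable error would then be 2.0% + 0.5% = 2.5%, the usual figure.
- **A reader might infer that 3.0 of the 5.0 points are a defect of this rule.** Of these, 1.5 + 0.5 = 2.0 points are the unfavourable tail that any two-sided 5% test has. Only the 1.0 point with discordant stages is specific to this rule.
- **A reader might infer that a significant stage I result for control would be announced as success.** The table's wording permits it, but the superiority framing and the reported MW would largely catch it. Continuing after a trend towards control (13.5% under no effect, about 0.18% at MW = 0.55 and N = 1745) is not an error in itself, since a two-sided test may leave room to show harm.

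The discordant case is not answered. The rejection has already happened when MW is reported, and nothing in the article makes the claim, or the opening of the secondary outcomes, depend on the pooled sign. Taking the pooled sign would not settle it either. Reversing both signs in the example gives a pooled Z of +0.74, still a rejection, on almost no overall evidence. A directional hypothesis in the missing figure would conflict with tables headed two-sided.

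**Conclusion.** The stage II rule is wrong as written: it can declare efficacy when the stages contradict each other, even when the pooled evidence favours control. The size is 1.0 percentage point under no effect, half of all stage II rejections. It is about 0.15% at MW = 0.55 and N = 1745, so the fault matters mainly if the true effect is null or small. The stage I labels are a milder fault of wording.

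The null split rests only on independent stages and uniform p-values. The figures at MW = 0.55 rest on the Noether approximation without ties at 1:2 allocation. The statistical analysis plan is not shown and may define p1 and p2 differently. The article presents these tables as the formal decision structure, so they need correcting in any case.

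**What to change.** **Preferred.** Define p1 and p2 as one-sided p-values for MW > 0.5 and run Bauer-Köhne at one-sided alpha 0.025. With α0 = 0.15 the bounds are α1 = 0.0166 and αc = 0.0038. Any stage I result favouring control then stops for futility. If a claim of inferiority is also wanted, add the mirror-image one-sided test, which keeps the two-sided level at 0.05. Replace both tables, and restate α0 and the power calculation under item f of Sample Size, because N = 1745 was derived with α0 = 0.3.

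**Minimal alternative.** Keep the present bounds. Allow an efficacy claim, and the move to the secondary outcomes, only if MW > 0.5 at stage I, and in both stages if stage II is run. This is slightly conservative: the favourable-direction error is 1.5% + 0.5% = 2.0% instead of 2.5%.

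**Cost.** Neither version needs more patients. The preferred one requires new tables and a rerun of the power calculation, and gains 1.5 to 2 points of power on the approximation above. The alternative requires one added condition.

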### Sample Size

As this is an observational study, the relations among effect size, sample size and power estimates are indicative only. However, some justification is needed to support the planning of the number of centers and the duration of the enrolment period.

Formal nonparametric sample size calculation was performed to allow detection of “small” group differences in the ordinal comparative effectiveness evaluations with 90% power.

The sample size calculations are based on the following design specifications:

a.Two-sided type I error defined as alpha=0.05 (multiple level alpha);b.90% power (1 – beta);c.Effect size measure for ordinal scales: Mann-Whitney measure of superiority (MW) [20–25, 38–40];d.Difference to be detected: MW=0.55 (equivalent to a “small” difference according to Cohen [26, 27]);e.Assumed maximum imbalance between enrolled groups: 1:2;f.Two-Stage Adaptive Design with α_0_=0.3; Stage I sample size=30% of total sample size (r_subsample I_=0.3); power compensation for defined two-stage parameters based on Newton Cotes-algorithm of fifth order [41];g.Nonparametric model: stochastic superiority (minimized assumptions).

In the presence of the above assumptions, the calculated total sample size results in 1745 subjects (including power adjustment for the chosen parameters of the two-stage procedure). For compensation of usual ambiguities (dropouts etc), the calculated sample size is enhanced by a factor of 1.15 (15%) from 1745 to a total of approx. 2000 subjects. This way, at least 90% power is guaranteed within the framework of the two-stage procedure.

Stage I is completed after enrollment of about 30% of the planned total patients (r_subsample I_=0.3).

Nonparametric sample size calculations within the framework of a Two-Stage procedure (Bauer-Köhne) [41] were based on the model of stochastic superiority and have been performed applying the validated software Nnpar 1.0 and Bauer-Köhne 4.0 from IDV Data Analysis and Study Planning, Krailling/Munich).

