#### Case-Mix Standardization

The patient groups are standardized using nonparametric multilevel stratification procedures combined with a “restricted cohort” design to minimize enrollment bias. The individual risk factors have been identified from previous research results on NIHSS predictor variables, allowing appropriate control for confounders of outcome after acute ischemic stroke. The pre-specified case-mix standardization strategy follows the recommendations of the GRACE Principles for Good Research on Comparative Effectiveness [4, 5].

Pre-Defined Clinical Predictor Variables [29]:

1.Initial NIHSS;2.Small Vessel Disease (yes-no);3.Prior Stroke (yes-no);4.Prior Diabetes (yes-no);5.Prior disability (yes-no);6.Age.

The operational definitions of variables no. 2 to 6 for consistent application across all participating sites are provided in the operational manual of the trial. The combination of the above variables is a highly efficient predictor for outcome after ischemic stroke [29], making an additional control of infarct volume dispensable due to comparable areas under the receiver operator characteristic (ROC) curves [29].

The top-level case-mix standardization is based on the initial NIHSS score as one of the strongest predictors for outcome after stroke [29–31]. The top-level control is performed by implementing stratification per NIHSS score unit with subsequent meta-analytic pooling of strata (i.e., comparing groups within identical baseline NIHSS score) (Figure 1). The eligibility restriction to NIHSS 8-15 allows full stratification for each possible baseline score (leading to a total of eight top-level strata).

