**Figure 1. F1:**
[figure not shown]
Case-Mix Standardization.

The pre-planned method for synthesis of the strata based on the primary Mann-Whitney (MW) effect size measure [20–25] is the Wei-Lachin test of stochastic ordering (one-dimensional test) [32], a maximin-efficient robust test (MERT) [33, 34] which provides a combined MW estimate and test of overall treatment effect from the pre-defined ensemble of independent strata.

The second level case-mix standardization is performed to control further confounders (see pre-defined clinical predictor variables). It is implemented within each of the top-level NIHSS strata by means of nested sub-strata and subsequent adjustment through the Cochran-Mantel-Haenszel (CMH) pooling procedure (also known as the van-Elteren procedure) [35]. The nested sub-strata are based on the following pre-defined clinical predictor variables (see above):

•Diabetes (yes-no);•Small Vessel Disease (yes-no);•Age (<65 – ≥65 years).

The combination of the three binary predictor variables results in a total of eight nested sub-strata. Technically the robust Peto-Wilcoxon test with CMH pooling of sub-strata was chosen, providing adjusted MW across sub-strata with associated confidence intervals. This procedure allows unbiased adjustment of ordinal or binary data also in the presence of very low sample sizes (only sub-strata with total N<3 are excluded from CMH analysis).

In addition to the specified multilevel case-mix standardization, controlling four out of the six pre-defined predictor variables, a specific method to strengthen observational, non-interventional studies is introduced for control of the two remaining confounders (“prior stroke” and “prior disability”): the “restricted cohort” design, i.e., patients are only eligible for this trial without prior stroke and prior disability. Restricted cohort design is one of the measures recommended for high-quality comparative effectiveness research [19]. This way, any risk of bias associated with the specific confounders can be avoided.

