The advantage of the chosen multilevel case-mix standardization compared to other, model-based approaches such as regression models is that any assumption about the nature of risk-outcome relation is avoided, allowing true *like-to-like* comparisons. Furthermore, some potential drawbacks of other procedures, as the model-based propensity score matching with its risk of bias due to incomplete matching [53], are reduced.

According to the Principles for Good Research on Comparative Effectiveness (GRACE) recommendations, the study size intended for the observational trial “should be described including a description of how that size was determined, what specific assumptions are being made, and how well these assumptions are supported”. As this is an observational study, the relations among effect size, sample size, and power estimates are indicative only. However, some justification is needed to support the planning of the number of centers and the duration of the enrolment period. Thus, within the framework of the chosen study design, we performed a fully elaborated sample size calculation based on the pre-specification of the analytical techniques.

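### The 90% power promised at 1745 subjects is not the power of the specified stratified two-stage analysis, which stays below 90% at that size in every scenario tested

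*Protocol article*

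**What the plan says.** The target in the Sample Size section is: "Formal nonparametric sample size calculation was performed to allow detection of “small” group differences in the ordinal comparative effectiveness evaluations with 90% power". Seven inputs follow: "Two-sided type I error defined as alpha=0.05 (multiple level alpha"), 90% power, the Mann-Whitney (MW) measure, "Difference to be detected: MW=0.55", a 1:2 group imbalance, a two-stage design with futility bound 0.3 and 30% of patients in stage I, and a stochastic superiority model. The result is that "the calculated total sample size results in 1745 subjects (including power adjustment for the chosen parameters of the two-stage procedure"). A factor of 1.15 takes it to about 2000. The section calls its power figures a guide only, yet ends by promising at least 90% within the two-stage procedure. The Discussion adds: "we performed a fully elaborated sample size calculation based on the pre-specification of the analytical techniques".

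Case-Mix Standardization defines the analysis. There is one stratum for each NIHSS score from 8 to 15, "leading to a total of eight top-level strata". Within each: "The combination of the three binary predictor variables results in a total of eight nested sub-strata". These sub-strata are pooled by CMH (van Elteren), and "only sub-strata with total N<3 are excluded from CMH analysis". The eight NIHSS strata are then combined by the Wei-Lachin test. The scheme applies to every effectiveness comparison.

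Two-Stage Procedure sets the rules, all labelled two-sided: success at stage I if p1 ≤ 0.0299, futility if p1 ≥ 0.3, otherwise success at stage II if p1 × p2 ≤ 0.0087.

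**The concern.** None of the seven inputs refers to strata, cell frequencies, prognostic strength or pooling weights, and the only adjustment named is for the two-stage parameters. The test that decides the trial compares patients only within 8 × 8 = 64 cells, drops very small cells, gains nothing from cells holding one group only, and pools in two steps, separately at each stage. The stated power has not been shown to belong to that test.

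Stage I matters most. It has the fewest patients per cell, and p1 alone decides whether the study stops for success, stops for futility or continues. If true power is well below 90%, a study with the planned effect is more likely to stop early or miss significance than the reader is told.

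**Working it through.** **1. The plan's own figure.** The fixed-sample two-group (Noether) formula with the stated inputs gives N = (1.960 + 1.2816)² / (12 × 1/3 × 2/3 × 0.05²) = 1576. The ratio 1745/1576 is 1.107. The stated two-stage rule does not lead from 1576 to 1745 (step 2). Values near 1745 appeared only when a stated input was changed: 1748 with stage I at 50% and one-sided alpha 0.025; 1757 with 1:1 groups and the futility stop ignored. So 1745 was not reproduced. The bounds are consistent with alpha: 0.0299 + 0.0087 × ln(0.3/0.0299) = 0.04996.

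**2. Two-stage power without stratification.** The expected z-value for n patients is 0.05 × √(12 × 1/3 × 2/3 × n).
- Stage I, n = 0.3 × 1745 = 523.5: 1.868. Stage II, n = 1221.5: 2.854.
- Critical z for p1 = 0.0299 is 2.171, and for p1 = 0.3 it is 1.036.
- Success at stage I: Φ(1.868 − 2.171) = 0.381.
- Not stopped for futility: Φ(1.868 − 1.036) = 0.797. This caps power at about 80% however strong stage II is.
- Success at stage II, integrating P(p2 ≤ 0.0087/p1) over the continuation region: 0.361.
- Total: 0.381 + 0.361 = 0.742.

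The same steps give about 80% at N = 2000, and 90% needs about 2817.

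**3. Cell sizes.** Stage I averages 523.5/64 = 8.2 patients per cell (600/64 = 9.4 if 2000 are analysed). The article gives no cell frequencies. Assume diabetes 25%, small vessel disease 20%, age under 65 40%. With a flat NIHSS distribution the rarest cell then expects 523.5/8 × 0.25 × 0.20 × 0.40 = 1.3 patients, below the exclusion limit.

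**4. Simulated power of the specified analysis, N = 1745.** Further assumptions: seven-level mRS, 1:2 groups, cells with N<3 dropped, van Elteren within each NIHSS score, equal Wei-Lachin weights across the eight scores, stated stage rules. The NIHSS distribution is flat, declining (18% at score 8 to 8% at 15) or steep (24% to 5%). R² is the share of latent mRS variance explained by the strata.

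| NIHSS | R² | Meaning of MW = 0.55 | Unstratified | Specified |
|---|---|---|---|---|
| flat | 0 | within cell | 75% | 68% |
| declining | 0 | within cell | 75% | 64% |
| steep | 0 | within cell | 75% | 54% |
| flat | 0.13 | marginal | 77% | 75% |
| flat | 0.25 | marginal | 77% | 81% |
| flat | 0.38 | marginal | 78% | 86% |
| declining | 0.25 | marginal | 77% | 76% |
| declining | 0.37 | marginal | 77% | 82% |
| steep | 0.35 | marginal | 74% | 69% |

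Each row used 2500 to 6000 runs, with an error of about 1 point. Separate simulations with other cell frequencies agreed. With no prognostic effect they gave 74% against 68% (equal cells), 75% against 66% (mildly uneven), 75% against 61% (moderately uneven) and 75% against 50% (steeply uneven). The lowest value in any scenario was about 47%. At N = 2000 those four settings gave 74%, 73%, 68% and 58%, against about 80% unstratified.

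**The case against.** Several objections carry weight.

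- **A fixed cost of stratification.** A reader might infer that stratifying costs a set number of points. The documents do not support this. The sign depends on stratum sizes, prognostic strength, whether MW = 0.55 is marginal or within stratum, and the Wei-Lachin weights; none is stated. The article itself calls the variables strong predictors, and strong predictors can raise power.
- **The source of the shortfall.** Most of the gap to 90% is already present without stratification and comes from the stage rule. For a fixed sample of 1745 the stratified test has about 92% (flat), 90% (declining) and 83% (steep). But the promise is made for the two-stage procedure, so this does not rescue it.
- **An unstratified origin of 1745.** This is a natural inference from the inputs, but the article does not say so and the figure cannot be reproduced from them.
- **Figures offered as a guide only.** This caveat is fair for an observational study, but it cannot stand beside a guarantee in the same section.
- **Changing the primary test.** A reader might conclude that Wei-Lachin should give way to one van Elteren pooling over 64 cells. With a constant effect and a declining distribution van Elteren does better (70% against 64%). If the latent effect rises from 0.6 to 1.6 times across NIHSS 8-15 (an assumption), Wei-Lachin does better: 70% against 66% without prognosis. The article chose Wei-Lachin for robustness and fixed it before enrolment. The case for replacing it is not made.

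**Conclusion.** The point holds as a misstatement of power. The inputs show no allowance for the specified analysis, so neither the 90% promise nor the Discussion's claim is supported. Under the stated two-sided rules, power at 1745 is about 74% without stratification and roughly 47-86% for the specified analysis across all scenarios tested.

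The separate effect of stratification runs from a gain of up to about 9 points to a loss of 20 or more; it is about a 6-12 point loss when the strata are not prognostic and NIHSS is flat or declining. These figures rest on assumed cell frequencies, prognostic strength and equal Wei-Lachin weights. The 74% needs only the stated inputs and the normal approximation. If the p-values were read as one-sided, against the article's own labels, unstratified power would be 85.0% (alpha 0.025) or 88.1% (alpha 0.05), still under 90%.

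The claim of less than 90% in every scenario is made for 1745, the number the plan itself ties to 90%; the strongest prognostic scenarios were not run at 2000.

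**What to change.** In the Sample Size section, replace the promise of at least 90% with the simulated power of the analysis as specified: 64 cells, the small-cell exclusion, van Elteren then Wei-Lachin, and separate stage p-values. Show the assumed cell frequencies and prognostic strength as a range, say whether MW = 0.55 is marginal or within stratum, and state the Wei-Lachin weights. Give the unstratified two-stage power beside it, so that the effects of the stage rule and of stratification can be told apart. Correct the Discussion sentence to match.

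Enrolment and the pre-specified Wei-Lachin primary test do not change. A 64-cell van Elteren pooling may be shown as a sensitivity analysis only. The cost is a simulation, a few sentences and a less favourable stated power.

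### The stated futility rule caps power at about 80% (1745 patients) or 83% (2000), so the guaranteed 90% is really about 74% to 80%

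*Protocol article*

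**What the plan says.** The Two-Stage Procedure section of the protocol article adopts the Bauer-Köhne design with two-sided p-values: "With a global multiple level alpha=0.05 two-sided, and defined futility level of α_0_=0.3 the following decision structure will be formally established". The stage I table stops the trial with success at "p_1_≤α_1_=0.0299" and says "stop because of futility" at "p_1_≥α_0_=0.3". Otherwise stage II follows, and the null hypothesis is rejected if the product of the two p-values is at most 0.0087. The same section says that the procedure "shows only a negligible loss in test power as compared to a fixed sample size study".

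The Sample Size section lists the planning inputs:

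- "Two-sided type I error defined as alpha=0.05 (multiple level alpha")
- 90% power
- Mann-Whitney effect (MW) of 0.55
- a maximum imbalance of 1:2
- "Stage I sample size=30% of total sample size"

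It arrives at 1745 subjects, said already to contain the adjustment for the two-stage parameters. It multiplies by 1.15 to reach about 2000 and concludes: "This way, at least 90% power is guaranteed within the framework of the two-stage procedure".

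**The concern.** A futility bound of two-sided p = 0.3 is strict when only 30% of the patients have been observed. A trial with a real effect of the planned size can easily show p above 0.3 at that point, and every such trial is lost for good. The share lost this way sets a ceiling on power that does not depend on stage II. If that share exceeds 10%, then 90% power is impossible, whatever adjustment the software made.

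At stake is how a negative outcome would be read. A futility stop after about 600 patients, or a failed stage II, would be taken as fairly strong evidence against an effect that the design was said to detect nine times in ten.

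**Working it through.** **Inputs**, all from the Sample Size and Two-Stage Procedure sections: two-sided p-values; MW = 0.55; allocation 1:2, so t = 1/3 and t(1−t) = 2/9; stage I fraction 0.3; α0 = 0.3, α1 = 0.0299, αc = 0.0087; N = 1745 or 2000.

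**1. The boundaries are correct.** The overall level is α1 + αc·ln(α0/α1) = 0.0299 + 0.0087·ln(0.3/0.0299) = 0.04996. So α1 = 0.0299 is valid only because trials with p1 ≥ 0.3 stop. The futility rule is binding.

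**2. Fixed-sample size (Noether).** N = (1.960 + 1.2816)² / (12 · 2/9 · 0.05²) = 1576. The stated 1745 is 1.107 times this, so the allowance for the two-stage rule was about 11%.

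**3. Expected stage statistics.** E[Z] = 0.05·√(12 · 2/9 · n).

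- N = 1745: stage I has n = 523.5, so E[Z1] = 1.868. Stage II has n = 1221.5, so E[Z2] = 2.854.
- N = 2000: stage I has n = 600, so E[Z1] = 2.000. Stage II has n = 1400, so E[Z2] = 3.055.

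**4. Futility stops under the planned effect.** Two-sided p1 ≥ 0.3 means |Z1| ≤ 1.036.

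- N = 1745: Φ(1.036 − 1.868) − Φ(−1.036 − 1.868) = 0.201. Power cannot exceed 79.9%.
- N = 2000: the stop probability is 0.166. Power cannot exceed 83.4%.

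**5. Full power.** Power = P(p1 ≤ 0.0299) + the integral, over 0.0299 < p1 < 0.3, of P(p2 ≤ 0.0087/p1), by numerical integration.

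| Analysed N | Success at stage I | Futility stop | Success at stage II | Power | Single-stage power |
|---|---|---|---|---|---|
| 1745 | 38.1% | 20.1% | 36.3% | **74.4%** | 92.7% |
| 2000 | 43.2% | 16.6% | 36.4% | **79.6%** | 95.5% |

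The loss against a single-stage test of the same size is 18 points at 1745 and 16 points at 2000.

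**6. Variants.**

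- *Ties:* a simulation with a seven-level mRS-like outcome (assumed category shares, tie-corrected Wilcoxon test) gave about 75.5% at 1745 and 80.6% at 2000.
- *1:1 allocation:* 78.9% and 83.7%.
- *No futility stop:* 87.6 to 87.9% at 1745.
- *Same bounds on one-sided p-values:* 88.1% at 1745 and 91.2% at 2000.
- *What 90% would take under the stated rule at 1:2:* about 2810 analysed patients, or an MW of about 0.563 (N = 1745) or 0.559 (N = 2000).

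**The case against.** - **The power figures are described as a guide only, because the study is observational.** True, and this lowers the weight of the claim compared with a randomised trial. But the same section reports a formal calculation with a two-stage adjustment and ends in a guarantee. The caveat does not cover a figure that its own inputs rule out.
- **The 1:2 ratio is a worst case, and 1745 is the number before the dropout allowance.** This also stands, so the fair statement is a range. The most favourable corner, 1:1 with all 2000 analysed, gives 84%. If losses use up the allowance at 1:2, the figure is 74%.
- **The p-values may have been meant as one-sided.** That reading comes closest to 90%, and a mismatch of sidedness between software and text is a possible origin, though this is an inference. It contradicts the two-sided decision tables, falls short at 1745, and would mean a one-sided level of 0.05.
- **Stage II could be enlarged.** Trials already stopped at stage I cannot be recovered. With 524 patients in stage I the ceiling stays at 80%.
- **The remark about a negligible loss describes the procedure in general.** Fair: it rests on a cited source and comes before α0 is set. The valid criticism is that it does not carry over to the parameters chosen here.
- **The strict futility bound is deliberate, given the limited number of patients for stage II.** That is a legitimate choice. What is wrong is the power attached to it.

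**Conclusion.** The concern holds. Under the plan's own inputs, power at MW = 0.55 and 1:2 allocation is about 74% with 1745 analysed patients and about 80% with 2000, against at least 90% stated. Across the two sample sizes and the two allocations the range is 74 to 84%. The false-negative risk at the planned allocation is 20 to 26%. Type I error control is not affected.

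The figures rest on the normal approximation with Noether's variance. They do not model the planned stratified pooling, so the decimals are approximate. The tied-data check moves them by about one point, far less than the gap to 90%.

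**What to change.** **Correct the statement (wording only).** In the Sample Size section, give power for MW = 0.55 at 1:2 as about 74% (1745 evaluable) or 80% (2000 evaluable), state the probability of a futility stop under that effect (20% or 17%), and remove the guarantee. In the Two-Stage Procedure section, say that the negligible loss does not apply with α0 = 0.3 and stage I at 30%, or drop the remark. Check whether the software was run with one-sided p-values.

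**If about 90% power is to be kept with the planned enrolment**, the parameters must be changed before stage I data are analysed. Two examples:

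- *One-sided p-values at level 0.025, α0 = 0.5, α1 = 0.0102, αc = 0.0038.* The level is 0.0102 + 0.0038·ln(0.5/0.0102) = 0.0250. Power is 89% at 1745 and 93% at 2000. The cost is fewer early futility stops: expected N of 2000 under no effect rises from 600 + 1400·(0.3 − 0.0299) = 978 to 600 + 1400·(0.5 − 0.0102) = 1286.
- *Stated boundaries, with stage I at 60% of patients.* Power is 91% at 2000 but 86.6% at 1745. Expected N of 2000 under no effect is 1200 + 800·(0.3 − 0.0299) = 1416.

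Neither option secures 90% if losses use up the whole dropout allowance, so the power statement should name the number of evaluable patients it assumes. If stage I has already been analysed, only the corrected statement is open, and a futility stop or negative result should be interpreted against 74 to 80% power.
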